#### Primary outcomes

Change over time (T1 and T2 and longer term T3) in the Approaches to Dementia Questionnaire will be examined with a repeated measures mixed-effects model, and the extent to which proximity to the participant in the intervention influences attitudes.

#### Secondary outcomes—suggestions

This will examine the types of changes (if any) that are reported in their friend/client/family member and the relationships between these and attitudes towards dementia.

### Study sample 3: art practitioners and other staff/professionals

To examine contagion effects, across all sites up to nine arts practitioners (and their organisations) involved in the intervention will be invited to take part. Up to nine participants in the geographic locations in which the interventions are delivered (eg, residential care homes, art galleries, NHS assessment unit, villages) will be purposively selected on the basis of a high level of engagement with the project compared with others in the locations, for example, care staff attending art sessions. This will involve an electronic survey, collecting the information described in table 1.

**Table 1 BMJOPEN2016011634TB1:** Data collected from art practitioners, staff/professionals

Art practitioners	Staff/professionals
Demographic data, including *professional age* measures how long the artist has been practising with people with dementia. *Number of journals* an artist receives or subscribes to as a measure of media exposure; *number of conferences attended in the last year as* a measure of network exposure; artists with *an honorary position* in their hospital/local authority; *artistic orientation*, coded as ‘1’ if the artist agrees with the statement that it is more important for an artist to ‘keep herself/himself informed of new artistic interventions than to devote time to practising art’ and ‘0’ otherwise.	Demographic data, including attitudes, beliefs and knowledge about people with dementia (Approaches to Dementia Questionnaire)^38^

Discussion and collaboration network data (adapted from Coleman *et al*,^39^ and Kahn and Antonucci,^40^ to be developed by researcher).

The perceived benefits of the intervention.

Self-reported leadership (adapted from Childers,^41^ to be developed by researcher).

Further waves of data collection will take place with (1) artists and (2) other professionals, for example, care staff, identified through the discussion and collaboration networks.

### Analysis of study sample 3

Indegree centrality scores are calculated for both samples. This is the number of other artists/practitioners who nominate or ‘send network ties to’ a particular artist/practitioner, and likewise the number of other colleague/relative/friends who nominate or ‘send network ties’ to other relatives/friends. Indegree centrality is computed for each person separately in the collaboration, discussion and total network (in the latter, indegree is the sum of the indegree in the collaboration and discussion networks). Indegree centrality is the most basic measure of status or prestige in a network. Since we will measure the social ties as pertaining to collaboration and discussion of the intervention with others for artists, those with greater indegree centrality are both ‘social connectors’ and recognised ‘experts’. Using these data, we will document how sociometric leadership, self-perceived leadership inter-relate in affecting social contagion effects concerning the intervention, and beliefs about dementia.

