To develop a theoretically informed visual arts intervention;To examine the impact of the visual arts intervention on the social connectedness, QoL and well-being of people living with dementia;To examine family and professional carers attitudes towards dementia, and whether they change through their exposure to the visual arts intervention;To examine the cost–benefit of the visual arts intervention;To explore qualitative changes in social connectedness and communication at the microlevel between the participant and formal or informal carer(s) and other network members;To undertake public engagement activities, challenging perceptions of dementia;To understand the implementation of arts and health research, exploring the extent to which ‘messages of change’ spread through professional networks—social contagion;To maximise the impact of the study for policy, practice and further research.

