### Public engagement

Public engagement projects using the work from Dementia and Imagination are under development. These will be highly interactive with a national, strategic focus and regional activity. An example of the activities is given below in table 2.

**Table 2 BMJOPEN2016011634TB2:** Example of public engagement activities

Activity/project title	Engagement questions	Outcomes/output	Target of activity	Data
Practising imagination through visual art	How can I have fun with my clients/spouse/partner? How can I learn more about helping someone living with dementia? How can I learn what a person with dementia is capable of? What are the best ways of using visual arts to enrich the lives of those with dementia?	Each of the 3 sites to run practitioner workshops/training sessions, using ‘A Practitioners Guide to Dementia and Imagination’ and online resources	More people delivering arts activities as part of care for people living with dementia Developing skills for those working in the care of people living with dementia, including family carers	Short evaluations; longer term follow-up to ascertain practice changes

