### Ethics and dissemination

All participant information provided is prepared in an acceptable manner that is clear and understandable. Bilingual information (Welsh and English) is prepared in Wales. All research staff and artists who will have direct contact with participants will undertake a programme of training developed by the research team. This will cover the MCA, informed consent, dementia awareness and the study protocol procedures, including data collection methods and data management. Professional standards as set out in the Research Councils UK (RCUK) Policy and Guidelines on Governance of Good Research Conduct are adopted by the study.

A requirement of UK research councils is that data resulting from the study are shared with the wider research community through the UK Data Archive. Data management protocols will be followed to ensure confidentiality and anonymity and protection of personal data. All data will be anonymised and stored separately from any identifying details. For contact purposes, these are linked through a unique identifier. Hard copy data will be stored securely in locked filing cabinets and electronically in password-protected folders. Access will only be available to the research team. The lead investigator will coordinate the sharing of data within the research team. Any transmission of data/transcripts will be through a secure method and encrypted. In terms of digital data (film/photography/audio) all qualitative interviews will be recorded using digital recording devices and securely stored as audio files (mp3) and encrypted.

Two types of visual data will be obtained. One is through videoing the observation sessions, and is purely for research purposes only. This will be securely stored through networked security. The other is artistic output, which will be handled sensitively, with the wishes of the participant being observed at all times. This will be securely stored and its use managed through the research team. Copyright will be held with specific investigators in the research team at each of the three data collection sites (as they are the employers).

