The research findings will be shared through a range of activities. International and national academic conferences and events will be attended to present papers and lead symposia. The project has developed an extensive public engagement and communication strategy to maximise the planned pathways to impact. This takes into account the variation in needs, concerns and preferred ways of working and communicating of each significant beneficiary group. Public engagement projects will target a broad range of stakeholders. A project website will be developed as a resource bank for stakeholders and a continuing legacy from the project. A quarterly newsletter will be produced. Policy and practice summaries will be developed from the findings. The current visual arts intervention protocol will be developed as a practitioners guide, freely available as an electronic resource as well as a hard copy version.

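### The sample 3 survey records no direct contact with the project, so for objective 7 spread between colleagues cannot be told apart from the project's own direct reach

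*Protocol article*

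**What the plan says.** Objective 7, in the list closing the Rationale, asks how far messages of change "spread through professional networks". Study sample 3 is the vehicle: "This will involve an electronic survey, collecting the information described in table 1".

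The artists' column of Table 1 includes journals "an artist receives or subscribes to as a measure of media exposure" and conferences in the last year as "a measure of network exposure". The staff/professionals column names demographics and the attitude questionnaire. The remaining rows cover discussion and collaboration networks, perceived benefits and self-reported leadership.

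The first wave is up to nine intervention artists (with their organisations) and up to nine people chosen for being highly engaged with the project. Later waves are people found through the networks those respondents report.

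Analysis of study sample 3 computes indegree centrality and then documents how sociometric and self-perceived leadership inter-relate "in affecting social contagion effects concerning the intervention, and beliefs about dementia".

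Elsewhere the article plans direct contact with people of this kind:
- development workshops for up to 40 stakeholders and artists (Intervention development);
- staff taking part alongside participants in some activities (Intervention development);
- training for research staff and artists, of which Ethics and dissemination says "This will cover the MCA, informed consent, dementia awareness and the study protocol procedures";
- a stakeholder website and a newsletter ("A quarterly newsletter will be produced", same section);
- as an example of public engagement, "Each of the 3 sites to run practitioner workshops/training sessions" (Table 2).

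**The concern.** A claim that beliefs or practice spread from person to person has to be set against a common external source. Here one obvious external source is the project itself. The team evidently accepted that outside exposure matters, since Table 1 measures journals and conferences. Those measures miss the project's own contact with respondents, and none is listed for staff.

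Colleagues in the same care home, ward or arts organisation may well share that contact. Two tied people who both attended sessions, or both read project material, would then hold similar views even if neither influenced the other. At stake is whether objective 7 can support a statement that good practice travels through professional networks, or only that connected people resemble each other.

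**Working it through.** The plan gives no figure on this point, so there is none to reproduce. The check compares the listed items with the planned contact, then illustrates the mechanism.

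**1. Items against routes of contact**

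| Direct route | Who is reached | Recorded in Table 1? |
|---|---|---|
| Art sessions | Artists; some care staff | No |
| Development workshops | Up to 40 stakeholders and artists | No |
| Project training | Research staff and intervention artists | No, but known by design for those artists |
| Newsletter, website | Stakeholders; recipients not named | No |
| Site workshops | Practitioners | No; probably after the survey |

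Sample 2 does record proximity to the participant in the intervention and relates it to attitudes. Sample 3 staff complete the same attitude questionnaire with no comparable item listed.

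**2. Where the gap falls.** The Abstract gives N=100 for the network analysis. If both ceilings of nine are totals across sites, the first wave is at most 9 + 9 = 18 individuals, leaving at least 100 − 18 = 82 for later waves. The article leaves some room on this count, because artists' organisations are also invited. Later waves are where spread would show.

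**3. Illustration by formula (every input assumed).** Half of professionals are reached directly; uptake is 50% if reached and 20% if not; there is no contagion. Let *h* be the share of ties joining people with the same exposure.

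- P(contact reached | contact adopted) = 0.5×0.5 / (0.5×0.5 + 0.5×0.2) = 0.25/0.35 = 0.714
- P(contact reached | contact did not adopt) = 0.5×0.5 / (0.5×0.5 + 0.5×0.8) = 0.25/0.65 = 0.385
- P(respondent reached) = h×p + (1−h)×(1−p), where p is 0.714 or 0.385
- P(respondent adopts) = 0.2 + 0.3 × P(respondent reached)

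| h | Respondent reached (contact adopted / not) | Respondent adopts (contact adopted / not) | Odds ratio |
|---|---|---|---|
| 50% | 0.500 / 0.500 | 0.350 / 0.350 | 1.00 |
| 80% | 0.629 / 0.431 | 0.389 / 0.329 | 1.29 |
| 100% | 0.714 / 0.385 | 0.414 / 0.315 | 1.54 |

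Within levels of the respondent's own exposure the ratio is 1.0, by construction.

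**4. Illustration by simulation.** N=100 and three sites come from the article. Everything else is assumed: four ties per person, all within site; no contagion; direct reach shifts attitude by *d* SD; attitude is regressed on the share of named colleagues reached; 1,000 replicates. The table shows the percentage of replicates with a contagion term significant at 5%, without an own-exposure item.

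| d | Reach 50/50/50% by site | 30/50/70% | 10/50/90% |
|---|---|---|---|
| 0.3 | 4.8 | 6.4 | 12.7 |
| 0.5 | 4.6 | 6.1 | 25.5 |
| 0.8 | 4.2 | 10.0 | 54.1 |

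With own exposure in the model, the rate is 4.0% to 6.2% in all nine cells and the mean coefficient is close to zero. The Monte Carlo standard error at 5% is √(0.05×0.95/1000) = 0.7 percentage points, so 6.1% and 6.4% are little different from nominal. Reach in this simulation depends on site alone, so a site term should also remove the inflation. It would not do so if reach clusters by home, ward or organisation within a site.

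**The case against.** Several points on the other side are sound.

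- **Training.** It is for research staff and artists, not care professionals. For the intervention artists it is universal, so an item on it would be constant among them.
- **Site workshops.** Public engagement belongs to the final stages. The workshops use a practitioners' guide, and the practitioners' manual is finalised only after data analysis. These workshops are unlikely to precede the survey.
- **Newsletter and website.** No recipients or start dates are given. That they reached respondents before the survey is an assumption.
- **First wave.** Selection itself makes these respondents' involvement broadly known.
- **Ties.** For artists, ties are defined by collaboration on and discussion of the intervention, which is closer to actual transmission than a generic tie. This helps, but it does not show that the talk rather than direct contact changed the view.
- **Format.** The article is condensed: the staff column is worded as not exhaustive, the network and leadership items are still to be developed, and qualitative data also feed the network analysis. Further items are not excluded. Even so, the article does state which exposures it measures and for whom, and that choice does not match objective 7.

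A reader might infer that people the project reached directly will be counted as reached through colleagues, or that the contagion result is biased upwards. The article supports neither. Its analysis section has no rule assigning anyone to a route, and inflation arises only if direct reach goes with ties.

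**Conclusion.** The point holds in a limited form. As listed, the sample 3 data cannot separate direct reach from spread between colleagues, mainly for later-wave respondents. Development workshops and session attendance carry the point best, because they do not depend on the late public engagement programme.

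Contagion may be overstated where direct reach clusters with ties. The size cannot be derived from the article. It is nil when reach is unrelated to ties, small in the simulation at moderate clustering (about 6% to 10% false positives), and large only under an extreme assumed split between sites (13% to 54%). The odds ratios of 1.29 and 1.54 likewise rest on assumed reach, uptake and tie patterns, and on an outcome and model the article does not specify. The change is worth making because it is cheap and bears on a named objective.

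**What to change.** At every wave, and for both artists and staff/professionals, add two or three dated yes/no items on direct contact with the project: attended an art session; attended project training or a workshop; received the newsletter or used the website. Dates allow contact after the survey to be set aside.

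In the contagion analysis, adjust for or stratify by the respondent's own direct contact. Report results among those without direct contact as a sensitivity analysis. They should not be the main evidence, because that would discard essentially the whole first wave and rest the objective on an unknown remainder of about 100 people.

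If the items are not added, report network associations and do not attribute them to contagion.

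The cost is a slightly longer electronic survey, parts of which are still to be developed, and one more covariate in a sample of about 100.

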^4^ However, the social representation of dementia often has a stigmatising effect on everyday interactions for both the person with dementia^21^ and their carer or partner. The general public often has a narrow and negative way of conceptualising dementia.^22^ In the face of this adversity, people with dementia (and their carers) can become disconnected, marginalised and excluded from society. Many people with dementia have minimal or no access to good quality intellectual or sensory activities, and those that do exist are often much below the person's level of functioning.^14^ This research examines the disconnection commonly experienced in dementia, and changes in social connectivity that can be facilitated by a stimulating visual arts intervention.

The stereotypes and stigma associated with dementia as previously described contributes to creating a pervasive, negative attitude known as excess disability, the tendency to attribute more disease or condition-associated impairment than the actual capabilities of the person with dementia.^23^ However, social networks have the potential for influencing behaviour and attitudes and this effect is described as social contagion.^24^ Thus, further aims of this research are to (1) use social network analysis to understand the social contagion through the implementation of good practice throughout the artists and practitioners involved in the project and beyond and (2) examine changes in perceptions and beliefs about people with dementia in the social networks of artists and professional carers of people with dementia.

The evidence review by the Mental Health Foundation^8^ noted that the community impact of arts activities has received little attention; however, activities have the potential to break down stereotypes, reduce stigmatising behaviour, foster social cohesion and raise awareness within the wider community. Creative outputs have the potential to counter stereotypes that often assume that people with dementia are unable to express their individuality in a way that is understood by others.^25^ Visual outputs can be used in creative ways to engage the public about health-related issues.^26^ Thus, public engagement activities will be a key focus in the final stages of the research.

The research programme addresses the following objectives:

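### Artists' network ties are defined by the intervention itself, so indegree mixes professional standing with exposure when contagion of the intervention is studied

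*Protocol article*

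**What the plan says.** Under Analysis of study sample 3, leadership is measured by nominations received: "Indegree centrality is computed for each person separately in the collaboration, discussion and total network", the total being the sum of the other two. The article states that "Indegree centrality is the most basic measure of status or prestige in a network". For artists it fixes what a tie is about: "we will measure the social ties as pertaining to collaboration and discussion of the intervention with others for artists". On that ground it reads artists with high indegree as connectors and acknowledged experts. It then plans to document how this sociometric leadership and self-perceived leadership "inter-relate in affecting social contagion effects concerning the intervention, and beliefs about dementia".

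Table 1 lists "Discussion and collaboration network data" as items still to be developed by the researcher from published instruments. It also lists perceived benefits of the intervention and a self-reported leadership scale. The Approaches to Dementia Questionnaire stands in the staff column only.

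Sampling starts from up to nine artists involved in the intervention and up to nine others chosen for high engagement with the project. Later waves are found through the discussion and collaboration networks.

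The objectives, at the end of the Rationale, ask how far messages of change "spread through professional networks—social contagion". The Rationale gives two contagion aims: to "understand the social contagion through the implementation of good practice throughout the artists and practitioners involved in the project and beyond", and to "examine changes in perceptions and beliefs about people with dementia in the social networks of artists and professional carers".

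**The concern.** An artist can be named as a partner in talk about the intervention only if that talk has taken place. A respected practitioner whom the project never reached will score near zero for want of exposure, whatever their influence among colleagues. The leadership measure thus carries part of what it is meant to explain.

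The sampling adds to this. The first respondents are chosen because they are involved or engaged, and later ones are reached along the same networks, so entry to the sample also follows exposure. Among the items listed for artists there is no record of uptake or practice change that is free of the tie question. Perceived benefits can be reported only by someone who already knows the intervention.

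At stake is the first contagion aim, the spread of good practice among artists and beyond. A positive association between leadership and spread could be read as influence flowing through prominent artists when it shows only where the project has been.

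**Working it through.** The document gives no sample-size derivation, effect size or scoring rule for the network analysis, so there is no figure to reproduce. The check has two parts.

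**1. Predictor and outcome side by side**

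- Predictor for artists: nominations received on ties about the intervention.
- Outcome, first half: contagion concerning the intervention. No scoring rule is given. The objective speaks of messages spreading, which overlaps with discussion ties. The Rationale speaks of implementing good practice, which does not have to.
- Outcome, second half: beliefs about dementia, a separate construct from tie counts.
- Other predictor: self-reported leadership, a scale not built from ties.

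Content is shared between intervention-specific indegree and the first half of the outcome, and nowhere else.

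**2. How much the shared content could matter**

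All inputs here are assumptions: n = 18, 50 or 100 people; random directed general ties with probability 5/n (about 5 per person); uptake of the intervention independent of all ties, so that true influence is zero; uptake prevalence p = 0.3, 0.5 or 0.7; an independent belief score; 1,000 replicates per setting. Ranges run over the nine settings.

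| Rule for a reported tie | Indegree compared with | Mean correlation |
|---|---|---|
| General ties | own uptake | -0.02 to 0.01 |
| Both parties engaged | own uptake | 0.72 to 0.79 |
| Only the nominator engaged | own uptake | -0.14 to -0.01 |
| Only the nominator engaged | number of engaged nominators | 1.00 |
| Both parties engaged | separate belief score | 0.00 to 0.01 |

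The value 1.00 is an identity, because the two quantities are the same count.

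The second row can be checked in closed form. With tie probability d, an engaged person's indegree has mean m = (n-1)dp and variance v = m(1-dp), and a non-engaged person's is 0. Then

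correlation = sqrt{ (1-p)m² / [(1-p)m² + v] }.

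For n = 100, d = 0.05, p = 0.5: m = 99 × 0.05 × 0.5 = 2.475; v = 2.475 × 0.975 = 2.413; (1-p)m² = 3.063; correlation = sqrt(3.063/5.476) = 0.75, which agrees with the simulated value.

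If a share r of the remaining ties is also reported, the rule is diluted. At the same n, d and p:

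- r = 0.25: the means are 99 × 0.05 × (0.5 + 0.125) = 3.094 and 99 × 0.05 × 0.25 = 1.238. Between-group variance is 0.25 × 1.856² = 0.861; within-group variance is 0.5 × (2.997 + 1.222) = 2.110. Correlation = sqrt(0.861/2.971) = 0.54.
- r = 0.5: the means are 3.713 and 2.475. Between-group variance is 0.25 × 1.238² = 0.383; within-group variance is 0.5 × (3.573 + 2.413) = 2.993. Correlation = sqrt(0.383/3.376) = 0.34.

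With zero influence the artefact can therefore be absent, moderate, large or total, depending on the tie rule and on what counts as spread.

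**The case against.** The article never scores contagion as talk about the intervention. The Rationale points to implementation of good practice and to beliefs, and the abstract to changes in perceptions and practice. Discussing something implies awareness, not uptake, since one can discuss it with a sceptic. The large correlations come from a rule that both parties have taken the intervention up, which the text does not state. This stands, and it is why no size can be attached to the trial.

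The tie definition is given for artists only, and its wording leaves open whether collaboration ties are more general than discussion ties. This also stands and limits the scope.

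Topic-specific leadership is a legitimate construct, stated openly, and general ties carry the opposite risk of counting contacts through whom the intervention never passed. That is fair, and it is a reason to keep the intervention-specific data. It does not make those data a suitable explanation for the spread of the same intervention.

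The full protocol or the survey instrument may define more. But the point rests on what the article states: the tie content, the reading put on it and the use made of it.

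A reader might infer that leadership and spread are linked by definition, so that the network analysis can neither support nor refute contagion. The document does not support this. The contagion outcome is left open, beliefs about dementia and self-reported leadership are measured apart from ties, and under one plausible tie rule the correlation with own uptake is close to zero.

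**Conclusion.** The concern holds in a limited form. For artists, indegree on ties about the intervention confounds professional standing with exposure when the outcome is contagion of the intervention, and sampling through engagement and through the same networks adds to this. An association between the two could appear without any influence.

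How strongly depends on the tie rule and on how contagion is scored, neither of which the article fixes. The simulated correlations rest on assumed density, prevalence and tie rules and should not be quoted as the trial's bias. The analyses of beliefs about dementia and of self-reported leadership are not affected by construction, and the point does not extend to the staff network on the wording given. It is a worthwhile and cheap improvement to a descriptive part of the study.

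**What to change.** In the network items still to be developed, or in later waves if the first is already in the field:

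1. Ask first for colleagues with whom the respondent discusses or collaborates on dementia or arts practice in general.
2. For each colleague named, ask whether the intervention was discussed.
3. Add an item on whether the respondent's own practice has changed.

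Use indegree on the general ties as the leadership measure for contagion of the intervention, and practice change as the spread outcome. Keep intervention-specific indegree as a description of diffusion, and do not read it as expertise or standing. If some waves used only the intervention-specific question, say so when interpreting them.

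The cost is a reworded name question, a nested follow-up and one further item, so a slightly longer electronic survey. The planned topic-specific data are retained.
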